## Abstract

**Background:**

Despite effective treatments, more than 30% of patients with diabetes will present with diabetic kidney disease (DKD) at some point. Patients with DKD are among the most complex as their care is multifactorial and involves different groups of health care providers. Suboptimal adherence to polypharmacy is frequent and contributes to poor outcomes. As self-management is one of the keys to clinical success, structured medication adherence programs are crucial. The PANDIA-IRIS (patients diabétiques et insuffisants rénaux: un programme interdisciplinaire de soutien à l’adhésion thérapeutique) study is based on a routine medication adherence program led by pharmacists.

**Objective:**

The aim of this study is to define the impact of the duration of this medication adherence program on long-term adherence and clinical outcomes in patients with DKD.

**Methods:**

This monocentric adherence program consists of short, repeated motivational interviews focused on patients’ medication behaviors combined with the use of electronic monitors containing patients’ medications. When patients open the electronic monitor cap to take their medication, the date and hour at each opening are registered. In total, 73 patients are randomized as 1:1 in 2 parallel groups; the adherence program will last 6 months in the first group versus 12 months in the second group. After the intervention phases, patients continue using their electronic monitors for a total of 24 months but without receiving feedback. Electronic monitors and pill counts are used to assess medication adherence. Persistence and implementation will be described using Kaplan-Meier curves and generalized estimating equation multimodeling, respectively. Longitudinal adherence will be presented as the product of persistence and implementation and modelized by generalized estimating equation multimodeling. The evolution of the ADVANCE (Action in Diabetes and Vascular disease: Preterax and Diamicron Modified-Release Controlled Evaluation) and UKPDS (United Kingdom Prospective Diabetes Study) clinical scores based on medication adherence will be analyzed with generalized estimating equation multimodeling. Patients’ satisfaction with this study will be assessed through qualitative interviews, which will be transcribed verbatim, coded, and analyzed for the main themes.

**Results:**

This study was approved by the local ethics committee (Vaud, Switzerland) in November 2015. Since then, 2 amendments to the protocol have been approved in June 2017 and October 2019. Patients’ recruitment began in April 2016 and ended in October 2020. This study was introduced to all consecutive eligible patients (n=275). Among them, 73 accepted to participate (26.5%) and 202 (73.5%) refused. Data collection is ongoing and data analysis is planned for 2022.

**Conclusions:**

The PANDIA-IRIS study will provide crucial information about the impact of the medication adherence program on the adherence and clinical outcomes of patients with DKD. Monitoring medication adherence during the postintervention phase is innovative and will shed light on the duration of the intervention on medication adherence.

**Trial Registration:**

Clinicaltrials.gov NCT04190251_PANDIA IRIS; https://clinicaltrials.gov/ct2/show/NCT04190251

**International Registered Report Identifier (IRRID):**

DERR1-10.2196/25966

## Introduction

Currently, approximately 463 million people have been diagnosed with diabetes worldwide [1]. In Switzerland, it is estimated that approximately 500,000 people have diabetes, representing 5.7% of the population [2,3]. Diabetes is associated with a burden of microvascular and macrovascular complications. Diabetic kidney disease (DKD), a microvascular complication of diabetes, affects 30%-40% of the patients with diabetes. Although DKD is the main cause of end-stage renal disease (ESRD), most patients will die of cardiovascular complications before reaching ESRD. Patients with DKD are among the most complex patients receiving diabetes care. Their care is multifactorial and multidisciplinary, involving different groups of health care providers. The multifactorial approach involves pharmacological treatment of various cardiovascular risk factors, including glucose levels, cholesterol levels, and blood pressure levels, and the pharmacological treatment of complications secondary to the reduced renal function. Patients with DKD often take more than 5 daily treatments. Polypharmacy is associated with suboptimal adherence, with risk of an accelerated decline in renal function and ESRD [4]. Although 40% of the patients with DKD do not adhere to their treatments [5,6], literature on medication adherence intervention programs addressing specifically DKD patients is scarce. Recent evaluations showed better metabolic and blood pressure control in patients participating in such programs [7,8]. Furthermore, a high level of self-management, including taking medications, increases the quality of life [6,9]. However, the results of most studies were not conclusive, as medication adherence was evaluated by subjective questionnaires with poor reliability. A feasibility study in patients with DKD who participated in an intervention combining a medication plan and regular phone calls by a specialist nurse did not demonstrate an increase in the medication adherence [10]. Another study concluded that intensive behaviors and interprofessional interventions delayed renal function decline [11]. However, to our knowledge, no study has evaluated the long-term impact of an adherence program or the optimal duration of such a program. It is necessary to better understand the needs of patients with DKD in terms of medication management to achieve better medication adherence and clinical outcomes and slow cardiovascular and renal disease progression.

In 1993, the pharmacy of Unisanté developed an interprofessional medication adherence program (IMAP) to support patients with chronic diseases with their drug management, combining the use of a medication event monitoring system (MEMS and MEMS AS, Aardex Group) and motivational interviews [12]. The first few studies showed encouraging results in improving medication adherence, clinical targets, and retention in care for chronically ill patients [13-18]. The PANDIA-IRIS (patients diabétiques et insuffisants rénaux: un programme interdisciplinaire de soutien à l’adhésion thérapeutique) study is based on this routine medication adherence program led by pharmacists. The global aim of this study is to evaluate the impact of the medication adherence program on long-term adherence and clinical outcomes in patients with DKD.

## Methods

### Ethical Considerations

The PANDIA-IRIS study was approved by the local ethical committee (Vaud, Switzerland) in November 2015. Since then, 2 amendments to the protocol version 4 have been accepted—in June 2017 and October 2019. This study is being carried out in accordance with the protocol and with the principles of the current version of the Declaration of Helsinki. The results of this study will be submitted to local, national, and international conferences and to a peer-reviewed journal for publication. This protocol has been written according to the SPIRIT reporting guidelines [19].

### Objectives

The primary objective of the PANDIA-IRIS study is to assess whether the length of the IMAP (12 vs 6 months) has an impact on medication adherence at 6, 12, 18, and 24 months after enrolment. As a secondary objective, this study will explore whether IMAP intervention changes the ADVANCE (Action in Diabetes and Vascular Disease: Preterax and Diamicron Modified-Release Controlled Evaluation) [20] and UKPDS (United Kingdom Prospective Diabetes Study) [21] clinical scores of patients with type 2 diabetes at 6, 12, 18, and 24 months after enrolment. Another secondary objective is to explore patient satisfaction with the medication adherence program through 30-minute semistructured qualitative interviews between an investigator and a subgroup of 14 patients included in the PANDIA-IRIS study. The main hypothesis is that patients participating in the 12-month adherence program will have better implementation and persistence, a higher long-term medication adherence rate, and better ADVANCE and UKPDS clinical scores at 12, 18, and 24 months after enrolment than patients in the 6-month intervention group.

### Trial Design

The PANDIA-IRIS design uses a mixed approach as it combines (1) a monocentric, prospective, and open randomized controlled trial and (2) a qualitative study. Patients will be randomized 1:1 in 2 parallel groups; patients of group A will attend the medication adherence program for 12 months and patients randomized to group B will attend the program for 6 months. Satisfaction with this study will be evaluated with selected patients through a qualitative interview at the end of the intervention phase or at the end of this study, or at drop-out (Figure 1). The legend for Figure 1 is available in Multimedia Appendix 1.

**Figure 1 figure1:**
[figure not shown]
Design of the PANDIA-IRIS (Patients diabétiques et insuffisants rénaux: un programme interdisciplinaire de soutien à l’adhésion thérapeutique) study.

### Enrolment of the Participants

This monocentric study is being conducted in the diabetes and kidney outpatient clinics in the University Hospital (CHUV, Lausanne, Switzerland), as well as in the outpatient clinic and the University community pharmacy of the Center for Primary Care and Public Health (Unisanté, Lausanne). The PANDIA-IRIS study is voluntary and each patient had to sign an informed consent form to be enrolled. Recruitment began in April 2016 and ended in October 2020. Eligible patients were identified each week through electronic database screening of all patients with diabetes followed in the University Hospital outpatient clinics. Investigators introduced this study to the eligible patients during a clinical appointment. Recruitment for the qualitative study began in July 2017 and ended in August 2020.

### Randomized Controlled Medication Adherence Study

The inclusion and exclusion criteria are presented in Textbox 1 and Textbox 2, respectively.

Inclusion criteria for the participants.Adults older than 18 years who are being followed in the University Hospital and have type 2, type 1, latent autoimmune diabetes in adults, or corticoid-induced diabetesOne of the following biochemical criteria: estimated glomerular filtration rate (eGFR)≤60 mL/min/1.73 sq m, eGFR>60 mL/min/1.73 sq m that has deceased >5 mL/min/year, urine albumin/creatinine ratio >30 mg/mmol, patients hospitalized at least twice for acute renal impairment in the past 5 years.Treatment with at least one of the following drug classes: oral antidiabetic drugs (metformin, dipeptidyl peptidase-IV inhibitors, sodium-glucose cotransporter-2 inhibitors, sulfonylureas, glinides), statins, diuretics, beta-blockers, calcium antagonists, alpha-blockers, angiotensin-converting-enzyme inhibitors, angiotensin II receptor blockers, or aspirin.Fluency in French or English. If not, the presence of an interpreter at each medication adherence visit.Full blood test (eGFR, glycated hemoglobin, albumin/creatinine ratio or total, high density lipoprotein and low-density lipoprotein cholesterol) in the 6 months prior to inclusion.

Exclusion criteria for the participants.Incapacity to make decisions, having cognitive disorders, or being under tutelagePregnancyActive cancer (not in the remission phase)Treatment of the patient is managed by nursing homes or home care servicesPatients already included in an intervention study

All the pharmacists providing the IMAP intervention were trained in motivational interviewing at the University community pharmacy of Unisanté [12]. The technicians were trained in how to complete the electronic monitor data, count pills, and use the MedAmigo software (MEMS and MEMS AS, Aardex Group) to upload electronic monitor adherence data and generate a medication adherence report.

### Qualitative Study

Semistructured interviews are conducted with a subgroup of 14 patients included in the PANDIA-IRIS study either at the end of the intervention phase so that the patient remembers the motivational interviews well or at the end of the study so that the patient can discuss the postintervention monitoring phase, or at drop-out. To ensure heterogeneity among the selected patients, patients meeting at least one of the following criteria will be enrolled prospectively: male, female, patients from group A, patients from group B, patients who completed the 24 months of the study, patients who just ended the intervention phase, patients who dropped out, and patients having an adherence rate >95% or <80%.

### Intervention

#### Use of the Electronic Monitor

In both groups, patients use electronic monitors for 24 months. Electronic monitors register the date and hour of each opening, which corresponds to the moment of the drug intake as long as both behaviors are consecutive. Nevertheless, one limitation of this tool is that patients could open the electronic monitor without taking the drug or swallowing it long after the electronic monitor opening. In order to limit this bias and before showing the electronic monitor data to the patient at each pharmacy visit, pharmacists check with the patients that each opening corresponds to the drug intake. They ask the patient about the usual lapse of time between each opening and the real time of the drug intake. The liquid-crystal display (LCD) screen on top of the electronic monitor cap resets at 3 AM each morning. Hence, each time the patient opens the electronic monitor cap, the LCD shows the number of cumulative openings until 3 AM on the next day. The LCD screen reminds the patient about whether the medication has been taken or not.

Drugs to monitor are prioritized based on the following algorithm, which we constructed based on side-effect profiles: (1) all oral antidiabetic drugs, (2) statins, (3) diuretics, (4) beta-blockers, (5) calcium antagonists, (6) alpha-blockers, (7) angiotensin-converting-enzyme inhibitors, (8) angiotensin II receptor blockers, and (9) aspirin. Moreover, in each class, eligible drugs taken more than once a day prioritize monitoring. The maximum number of monitored drugs is 6. Physicians can modify the treatments at any time. If a patient has to stop all the monitored drugs, he or she will stop the study but the data collected until then will be kept for analysis. If a drug is switched to another eligible drug, the new prescribed drug will be monitored.

#### Medication Adherence Intervention

All included patients will benefit from the IMAP in addition to routine clinical care. The frequency of IMAP visits is the same in both groups throughout the 24 months: once per month for the first 3 months, followed by 1 visit every 3 months (Figure 1). Pharmacists lead short, repeated semistructured motivational interviews based on the theoretical Fisher model [22]. First, patients’ knowledge of treatments is evaluated. Then, motivation to take the treatment, self-efficacy, daily medication behaviors, and side-effect management are explored in an empathetic nonjudgmental way. The graph representing electronic monitor daily openings (dates and hours) since the last visit is shown to the patient as feedback. Adherence results are discussed to reinforce acquired adherent behaviors and to understand nonadherent episodes, and then, solutions with tailored elements are constructed to address nonadherence. To ensure interprofessional collaboration, the pharmacist sends a semistructured report after each medication adherence interview to the clinical team, including the endocrinologist, nephrologist, general practitioner, nurse, dietician, and psychologist. During the COVID-19 pandemic, adherence interviews are conducted through phone calls for some patients, if the clinicians considered them at high risk of complications following infection by SARS-CoV-2. If the interview is conducted by phone, it is notified on the case report form.

#### Qualitative Study

At the end of the intervention phase or at the end of this study or at drop-out, patients are invited to express their opinions on the medication adherence program and the overall study. Patients who signed the informed consent form specific to the qualitative part of the PANDIA-IRIS study participate in 30-minute in-depth semistructured interviews. The main themes covered are the evaluation of the quality of the medication adherence interview, the positive and negative aspects of the program, the opinions of the patient regarding the electronic monitor, and if the patients completed this study, the perceived impact of the program during the 12-month to 18-month follow-up period.

### Postintervention Monitoring Phase

After the intervention phase, patients will still use electronic monitors with their LCD screens, but their adherence data will be double-blinded. Patients will not receive any feedback or motivational interviews about their daily drug management. The clinical team will not obtain any adherence reports. Due to ethical reasons, if the medication adherence rate detected by the MedAmigo software is less than 30% for at least one drug for 2 consecutive pharmacy visits, the software will automatically notify the pharmacist, and the patient will stop the study and will be oriented to the routine IMAP. If a physician in charge of a patient explicitly asks to access the adherence data during the postintervention monitoring phase for clinically urgent and important reasons, the principal investigator will sign a permission form that will be included in the case report form, and the patient will stop the study. All the data collected until then will be kept for analysis. At 18 months after the inclusion, during the postintervention monitoring phase, blood and urine samples will be collected to determine the clinical values at this time point. Indeed, the frequency of blood and urine samples collection differs between patients, and collecting laboratory values for each patient at this precise time point will ensure consistency in the analysis.

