#### Secondary Outcomes

The ADVANCE and UKPDS clinical scores will be assessed and compared at baseline, 6, 12, 18, and 24 months after enrolment for patients with type 2 diabetes in both groups. The ADVANCE score indicates the risk of developing cardiac complications associated with type 2 diabetes within 4 years and estimates the risk of developing renal complications within 5 years or more than 5 years. The UKPDS score calculates the risk of fatal coronary heart disease or stroke in patients with type 2 diabetes with no antecedent cardiovascular disease. These scores are calculated on the following parameters: sex, ethnicity, smoking status, time since diabetes diagnosis, blood pressure, glycated hemoglobin, total and high-density lipoprotein cholesterol, atrial fibrillation, albumin in urine, abdominal circumference, and BMI [24].

During the postintervention monitoring phase, the number of patients with less than 30% adherence for at least one drug during 2 consecutive visits as well as the time-to-event will be compared between the groups. We will also describe implementation and persistence at 6 months and 12 months after the end of the intervention in both groups to explore the impact of the length of the intervention on adherence. Patient satisfaction regarding the program will be analyzed through qualitative interviews.

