#### Participant Timeline and Data Collection

Data collection is performed by the investigators and is prospectively registered in the platform Research Electronic Data Capture (RedCap), a secure web app for building databases. Each patient has a unique study number generated by RedCap. First, during recruitment, if eligible patients refuse to participate, their reasons for doing so are recorded. For patients included in this study, their sociodemographic data are provided by the administrative software of the hospital at inclusion. Clinical data for each visit are provided by the patient electronic clinical file (Soarian, Cerner) and reported in the case report form. The participant timeline and data collection process are shown in Multimedia Appendix 2 [25] for both groups. Electronic monitor data are uploaded on the secured MedAmigo web portal at each medication adherence visit during the intervention and at each medication refill during the follow-up for both groups. Concomitantly, the patient’s electronic monitor use is systematically checked by the pharmacist through a set of validation questions (ie, identification of nonmonitored periods, eg, during hospitalizations, whether medication was sometimes prepared in advance for a later use since the last visit). A pill count is performed by the technician during the intervention phase and by a blinded independent researcher during the postintervention monitoring phase. The participants who leave this study before completion are not replaced and are considered as dropouts but the data collected until then will be kept for analysis. The data monitoring committee is composed of the main investigators of the PANDIA-IRIS study. After the end of this study analysis, data will be archived and kept for 10 years in the secure data warehouse of the University Hospital before destruction. The database of the PANDIA-IRIS study will be shared in a secured data repository of the University of Geneva (Yareta) at the end of the analysis.

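### Three exit rules end the whole study instead of only electronic monitoring, so later ADVANCE and UKPDS scores are lost although they do not need the monitor

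*Protocol article*

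**What the plan says.** The protocol article has three rules that remove a patient from the study.

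- **All monitored drugs stopped** (Use of the Electronic Monitor): "If a patient has to stop all the monitored drugs, he or she will stop the study". This applies from inclusion.
- **Adherence below 30%** for at least one drug at two consecutive pharmacy visits (Postintervention Monitoring Phase): "the patient will stop the study and will be oriented to the routine IMAP".
- **Urgent physician request for the adherence data** (same section): "the principal investigator will sign a permission form that will be included in the case report form, and the patient will stop the study".

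The first rule, and the paragraph containing the other two, say that what was gathered up to the exit is retained. Participant Timeline and Data Collection says of everyone who leaves early that they "are considered as dropouts but the data collected until then will be kept for analysis".

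The ADVANCE and UKPDS scores, for patients with type 2 diabetes, "will be assessed and compared at baseline, 6, 12, 18, and 24 months after enrolment" (Secondary Outcomes). The inputs listed there are demographic, clinical and laboratory items, and none is read from the electronic monitor. On their source, the article says: "Clinical data for each visit are provided by the patient electronic clinical file". For month 18 it adds that "blood and urine samples will be collected to determine the clinical values at this time point", so that every patient has values at that time.

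Missing Data says that missing values will be marked in the tables and uses an unclear verb for the rest, which most naturally means no imputation.

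**The concern.** Each event justifies ending blinded adherence monitoring: no drug is left to monitor, the blinding is broken, or the patient returns to the routine program. None of these reasons extends to blood pressure, glycated hemoglobin, lipids or urine albumin. The rules merge the end of monitoring with the end of follow-up.

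The main hypothesis under Objectives names the scores at 12, 18 and 24 months, which are the time points at risk. The loss is unlikely to be random, since one exit is defined by very poor adherence and another by clinical urgency. The article also plans to compare between groups "the number of patients with less than 30% adherence for at least one drug during 2 consecutive visits as well as the time-to-event", so one cause of lost scores is something the trial thinks may differ by arm. Under the two postintervention rules, group B is exposed for 18 months and group A for 12.

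The planned analysis does not clearly repair this. A standard unweighted GEE generally needs missingness unrelated to the outcome given the covariates. Adjusting for adherence, one of the listed covariables, conditions on a post-randomisation variable and so is not a comparison by randomised arm.

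**Working it through.** **No figure in the plan is contested.** The sample size supplies only the 36 per arm used below. It reproduces: the logit difference between 97.5% and 92.5% is 1.151, and with SD 1.7, two-sided alpha 0.05 and 80% power the usual formula gives 35 per group (70 in total, against 72 stated). A simulation with 365 daily measures per patient gives 79% power at 36 per group.

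**Which score visits a rule can remove.** There are four post-baseline score times: 6, 12, 18 and 24 months. A physician-request exit is possible only after the intervention phase. It can therefore remove up to three time points in group B (12, 18, 24) and up to two in group A (18, 24). The below-30% exit needs two consecutive visits and acts somewhat later. The stop-all-drugs exit is open from inclusion in both arms and has no built-in imbalance.

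**Illustration for the physician-request exit.** The article gives no exit rates, so these are assumptions:

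- a constant annual exit rate r, equal in both arms, of 5, 10 or 15%;
- 36 scored patients per arm, which is an upper bound because the scores apply to type 2 diabetes only (and UKPDS only to patients without earlier cardiovascular disease).

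Fraction lost by 12, 18 and 24 months:

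- Group A: 0; 1 − (1 − r)^0.5; r
- Group B: 1 − (1 − r)^0.5; r; 1 − (1 − r)^1.5

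Score visits lost per arm, of 4 × 36 = 144, are 36 × the sum of the three fractions.

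| r | Lost by 12/18/24 months, A | Lost by 12/18/24 months, B | Visits lost, A | Visits lost, B | Total of 288 |
|---|---|---|---|---|---|
| 5% | 0 / 2.5 / 5.0% | 2.5 / 5.0 / 7.4% | 2.7 | 5.4 | 8.1 |
| 10% | 0 / 5.1 / 10.0% | 5.1 / 10.0 / 14.6% | 5.4 | 10.7 | 16.2 |
| 15% | 0 / 7.8 / 15.0% | 7.8 / 15.0 / 21.6% | 8.2 | 16.0 | 24.2 |

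The ratio B to A is 1.95 to 1.99 in visits. In patients lost by month 24 it is about 1.5 (for example 7.4% against 5.0%).

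**Possible shift in the 24-month contrast.** If exiting patients' change in score is worse by a given gap, leaving them out moves each arm's mean by fraction lost × gap. The contrast moves by (fraction lost in B − fraction lost in A) × gap.

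- Gap 1 SD: 0.024, 0.046 and 0.066 SD at r = 5, 10 and 15%.
- Gap 0.5 SD: 0.012, 0.023 and 0.033 SD.

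The standard error of a difference in means with 36 per arm is √(2/36) = 0.236 SD. The largest shift is 0.066/0.236 = 0.28 standard errors. A GEE that also uses earlier visits may give a different shift.

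**The case against.** **The article never says outright that score collection stops.** This is true; it is inferred from the patient stopping the study and from the limit on which data are kept. The schedule in Multimedia Appendix 2 is not shown. But nothing in the visible text continues clinical follow-up, and the point rests on stated rules, not on missing detail. If the sponsor intends otherwise, one sentence settles it.

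**The effect is small and the outcome secondary.** This stands and limits how strongly the point can be pressed.

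**The planning figures suggest few below-30% exits.** With means of 97.5% and 92.5% and SD 1.7 on the logit scale, about 0.4% of group A and 2.4% of group B would have global adherence below 30%, or about 0.1 and 0.9 of 36 patients. That calculation uses adherence to all drugs averaged over the whole study. The trigger works on any single drug between visits, so the estimate does not bound it, and it says nothing about the other two exits.

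**The twofold ratio follows from the assumptions.** It does: it comes from equal rates and from counting visits. What the document fixes is the longer exposure in group B.

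**Post-exit scores do not fit the planned model and reflect later care.** The score model lists adherence as a covariable, and a group B patient sent back to the program receives it again. Both are real. The first needs a model for the arm comparison without adherence at that visit. The second is acceptable in a comparison by randomised arm, if disclosed.

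**The change comes late.** Recruitment ended in October 2020 and collection runs to October 2022, so some earlier exits may not be recoverable. Later ones are.

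**Conclusion.** The concern holds as an inexpensive improvement that should be made. As written, the three rules discard later ADVANCE and UKPDS values for reasons that concern only the monitor. The loss is plausibly informative and, for two of the rules, open for longer in group B.

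The actual size cannot be computed without exit rates. Under the assumed rates the gain is fewer avoidable losses more than removal of a large bias: the shift stays below 0.3 standard errors even at 15% per year with a 1 SD gap. The conclusion rests on the natural reading of the exit rules and on the missing-data sentence meaning no imputation. It concerns secondary outcomes in patients with type 2 diabetes and leaves the primary adherence comparison untouched. Confidence is medium.

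**What to change.** In Use of the Electronic Monitor and Postintervention Monitoring Phase, state that each of the three events ends blinded electronic monitoring and adherence counting from that date, but not clinical follow-up. Then:

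- unless the patient withdraws consent, keep collecting the score components from the hospital file at the remaining time points, and keep the planned 18-month sample for these patients;
- compare the scores by randomised arm in patients with type 2 diabetes, with a model that does not need an adherence value at that visit;
- report the exits and their reasons by arm.

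Physician access to the data and referral to the routine program stay as they are.

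The cost is an amendment, a consent check and continued score collection in a few patients. Because routine sampling frequency varies between patients, some components (laboratory timing, abdominal circumference) may be sparse outside month 18. Post-exit scores will include the effect of later care, such as a restarted program, and the report should say so.
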